### Statistical analysis.

An independent statistician will carry out the statistical analysis. He or she will have no knowledge of whether each participant belongs to one group or another, nor what type of treatment was implemented in each group. All necessary data will be extracted into an Excel spreadsheet and analysed using IBM® SPSS® Statistics 27.0.1.0.

A Kolmogorov-Smirnov test will be used to check whether or not the data fit a normal distribution. A descriptive analysis will be carried out to explore the variables related to the study.

Quantitative variables with parametric distribution will be assessed with a T-test or ANOVA, while if the distribution is non-parametric a Mann-Whitney test will be used. This analysis will examine whether there are differences between groups that may support or refute the hypothesis that strength training reduces hospital stay, ICU stay and/or complications in this type of patient. This analysis will also be used to test whether ventilation and respiration values as well as quality of life values are different in each group.

To assess whether there is an influence of confounding variables (BMI, toxic habits, comorbidities, underlying pathologies) on the direction of the dependent variables, multiple regression will be performed.

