#### Sample size.

For the primary outcome (time in the intensive care unit), an effect size of 0.613 was determined based on previous research on the effect of a multidimensional preoperative intervention in patients awaiting elective coronary artery bypass graft surgery (47). To obtain a statistical power of 0.8 with a 2-tailed alpha of 0.05 in a Student's t-test, considering a dropout rate of 10%, a total of 96 participants (48 subjects per group) were required.

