## **RESULTS**

The results will first be expressed taking into account hospital and/or ICU stay as the primary variable. Also, to address secondary variables with criteria, values related to postoperative complications and quality of life will be cited. This will be followed by values related to functionality and muscular and aerobic endurance. Finally, it will be reflected whether confounding variables may interfere with the direction of dependent variables.

Quantitative variables will be expressed in terms of means and standard deviations, provided that they comply with a parametric distribution, or in medians and interquartile ranges if this is not the case. Box and whisker plots shall be used for their graphical representation.

Categorical variables, corresponding to the EuroQoL-5D items, will be expressed in terms of frequency and percentages and bar charts will be used for ordinal variables, while nominal descriptive variables will be expressed using pie charts.

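### The multiple regression is framed as covariate influence on the outcomes, which is prognosis; it does not show whether the group comparison is confounded, and no adjusted group difference is requested

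*Protocol*

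**What the plan says.** The Protocol's Statistical analysis section starts with the between-group tests: "Quantitative variables with parametric distribution will be assessed with a T-test or ANOVA", or a Mann-Whitney test where the distribution is not normal. It says that this analysis is the one that will bear on the treatment hypothesis.

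The regression comes afterwards and has its own purpose. The sentence begins "To assess whether there is an influence of confounding variables (BMI, toxic habits, comorbidities, underlying pathologies" and ends "on the direction of the dependent variables, multiple regression will be performed".

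The Results section turns this into the last item to be reported: "Finally, it will be reflected whether confounding variables may interfere with the direction of dependent variables".

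In both places the thing being influenced is the dependent variable. Neither place mentions the difference between groups, an adjusted estimate, or what result would count as interference.

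**The concern.** The word confounding refers to the comparison between the two prehabilitation groups. A covariate confounds that comparison if it is related to the outcome and also differs between the groups, so that the estimated group difference moves when it is taken into account. The Protocol's wording covers only the first half, the relation to the outcome.

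Two things are at stake. First, comorbidity or BMI may well predict ICU stay. A report that follows the wording could then say that confounders interfere, although the groups are balanced and the treatment estimate would not move. Second, where chance imbalance does shift the estimate, the stated question does not call for the figure that would show it, namely the group difference after adjustment.

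The Design section calls the trial non-randomised and also says that participants are assigned at random. That contradiction is a separate matter, but until it is resolved an adjusted comparison matters more.

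**Working it through.** **Inputs from the Protocol (Sample size section).** Primary outcome ICU time: "For the primary outcome (time in the intensive care unit), an effect size of 0.613 was determined". Power and alpha: "To obtain a statistical power of 0.8 with a 2-tailed alpha of 0.05". Dropout allowance 10%. Total: "a total of 96 participants (48 subjects per group) were required".

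**Inputs assumed.** Four model terms, one for each named covariate domain (eight as a variation); independent, normally distributed covariates and normal errors; covariate R² from 0 to 0.36. The Protocol gives neither the number of terms nor any prognostic strength.

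**Step 1: the plan's own figure.** A two-sample t-test with d = 0.613, two-sided alpha 0.05 and power 0.80 needs 42.76, so 43 per arm. With dropout, 43 / 0.90 = 47.8, so 48 per arm and 96 in total. The stated size is reproduced, and about 2 × 43 = 86 patients are evaluable.

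**Step 2: what separates prognosis from confounding.** For least squares with group G and covariates Z₁ to Z₄:

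unadjusted group difference = adjusted group difference + Σ cⱼ × (mean of Zⱼ in the experimental group − mean of Zⱼ in the conventional group)

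Here cⱼ is the fitted coefficient of Zⱼ in the model that contains group. The shift needs both a non-zero cⱼ and an imbalance. The Protocol's question concerns cⱼ alone. With exactly equal covariate means the sum is zero for any cⱼ.

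**Step 3: how often covariates would look influential with no confounding present.** Arms exactly balanced, N = 86, four covariates with equal coefficients:

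| Covariate R² | At least one covariate p < 0.05 | Joint F test p < 0.05 | Adjusted minus unadjusted group difference |
|---|---|---|---|
| 0 | 18% | 5% | 0 |
| 0.05 | 54% | 34% | 0 |
| 0.10 | 78% | 64% | 0 |
| 0.20 | 97% | 95% | 0 |
| 0.30 | 100% | 99.8% | 0 |

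The first entry agrees with arithmetic: 1 − 0.95⁴ = 18.5%. With eight null terms it is 1 − 0.95⁸ = 33.7%.

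A second run used standardised coefficients of 0, 0.1, 0.2 and 0.3. R² is four times the squared coefficient: 0, 0.04, 0.16 and 0.36. At least one covariate was significant in about 18%, 47%, 92 to 93% and 100% of trials. With group also in the model the figures were 19%, 49%, 93% and 100%. Adding group therefore does not help if the covariate coefficients are what is read.

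**Step 4: what an adjusted estimate offers.** Arms allocated at random, N = 86, true d = 0.613. At R² = 0.20, adjustment moves the group estimate by more than 10% (an illustrative threshold) in 57% of trials and reverses its sign in under 1%. Power for the group effect goes from about 80% unadjusted to about 84% adjusted at R² = 0.16 and about 93% at R² = 0.36. If the covariates are not prognostic, adjustment costs 1 to 2 percentage points.

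**The case against.** The strongest reply is that the Protocol states no faulty test. It gives the regression one sentence, and model terms and reporting criteria are ordinary SAP content. The sentence follows the group comparison and calls the covariates confounders, which presupposes an exposure. A statistician could reasonably fit outcome on group plus covariates and obtain the adjusted effect without being told to. The regression is also supplementary and reported last.

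Much of this stands, and it limits what can be claimed. Three stronger readings are tempting, and the document does not support them:

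- A reader might infer that the regression tests only covariate effects. The text does not say that group is omitted, nor that covariate p-values are the criterion.
- A reader might infer that confounding would be reported almost always. That needs covariates explaining roughly 16 to 20% of outcome variance or more, and the Protocol gives no such figure. At R² = 0.05 the rate is 54% for any covariate and 34% for the joint test.
- A reader might treat the high rates as inflated type I error, as multiples of alpha. Where covariates are prognostic, the hypothesis of no association is false and those rates are power. Only the 18% at R² = 0 is an error rate, and it reflects four tests made at once.

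A change criterion is not a clean verdict either: the 57% in step 4 shows that modest shifts are common under random allocation. That is a reason to show both estimates and not to label covariates as interfering or not.

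The reply does not remove the point about the target. Model terms can be left to a SAP, but two sections of the Protocol state the question and the reported conclusion, and both concern the outcome. A SAP that followed them faithfully could report prognosis as interference.

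**Conclusion.** The point holds as a fault in the stated target of the analysis. A positive result for covariate influence on ICU stay or another outcome would not be evidence that the group comparison is confounded, and the Protocol requests no adjusted group difference that would be. The identity in step 2 establishes this without any assumption about prognostic strength.

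The size does depend on assumptions. If covariate significance were what was read, apparent influence under perfect balance would range from about 18% to over 90% of trials, depending on how prognostic four independent covariates are.

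The unadjusted primary test and the sample size are unaffected. The consequence is a potentially misleading statement in the report and an informative estimate left out, so this is a worthwhile correction at almost no cost and not a threat to the trial's main result.

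**What to change.** In Statistical analysis, replace the regression sentence with wording such as: *For ICU stay and each other quantitative outcome, the outcome will be regressed on treatment group and the named pre-operative covariates (BMI, toxic habits, comorbidities, underlying pathology). The adjusted group difference and its 95% CI will be reported beside the unadjusted difference. The influence of the covariates will be described by the change in the group difference, not by the covariates' p-values.*

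Take the unadjusted difference from the same model without the covariates, so that the two are on one scale even where the main test is Mann-Whitney.

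In Results, replace the sentence on interference with: *Adjusted and unadjusted group differences will be presented side by side.*

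The cost is two sentences. The data are already to be collected, the software is the same, and no patient or procedure is added. What is given up is a statement about which covariates interfere, together with the small loss of power shown in step 4 for the adjusted estimate if the covariates turn out not to be prognostic.

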#### Sample size.

For the primary outcome (time in the intensive care unit), an effect size of 0.613 was determined based on previous research on the effect of a multidimensional preoperative intervention in patients awaiting elective coronary artery bypass graft surgery (47). To obtain a statistical power of 0.8 with a 2-tailed alpha of 0.05 in a Student's t-test, considering a dropout rate of 10%, a total of 96 participants (48 subjects per group) were required.

#### Data collection

Sex, age, underlying pathology, comorbidities, body mass index (BMI) and toxic habits will be the descriptive variables collected in both groups. All these data will be stored in their clinical history and will be extracted by the person in charge of epidemiological data management at the hospital, who will include them in an Excel table, also indicating whether each participant survives or not, as well as the information related to the intervention and the pathology, catalogued using the International Classification of Diseases 11 (ICD-11) or the appropriate one if there are updates. Days of hospitalisation, intensive care unit (ICU) stay, if applicable, Charlson comorbidity index, and possible postoperative complications for each participant will also be reflected in this table.

Although the database from which the data will be extracted will not contain personal data, as each participant will receive a numerical identification code, all researchers will sign a data confidentiality commitment sheet prior to the start of the study, which states that patients' personal data will be protected.

The medical information of each participant and his or her evolution at each point of the measurement shall be recorded in his or her medical record.

## **RESULTS**

The results will first be expressed taking into account hospital and/or ICU stay as the primary variable. Also, to address secondary variables with criteria, values related to postoperative complications and quality of life will be cited. This will be followed by values related to functionality and muscular and aerobic endurance. Finally, it will be reflected whether confounding variables may interfere with the direction of dependent variables.

Quantitative variables will be expressed in terms of means and standard deviations, provided that they comply with a parametric distribution, or in medians and interquartile ranges if this is not the case. Box and whisker plots shall be used for their graphical representation.

Categorical variables, corresponding to the EuroQoL-5D items, will be expressed in terms of frequency and percentages and bar charts will be used for ordinal variables, while nominal descriptive variables will be expressed using pie charts.

## **DISCUSSION**

In order to provide a better understanding of the most appropriate treatment for patients undergoing heart valve surgery, this will be the first controlled clinical study focused on adding strength exercise as an additional treatment during prehabilitation. This variable will be compared to a protocol focusing on strengthening respiratory muscles and improving ventilatory capabilities, which have already been shown to be effective in people undergoing major cardiac surgery (9,12,15-17). To better understand the results, they will be carefully analysed, taking into account the special characteristics of the study sample. They will also be compared with the results reflected in other studies focusing on individuals with the same characteristics and focusing on similar objectives, albeit with other types of approaches. Therefore, future studies will be able to analyse our results and transfer the protocol to larger or different population groups.

The results of this study focus on helping to improve rehabilitation and prehabilitation protocols, considering that it is important to maintain pulmonary training, as well as the inclusion of peripheral exercises that help people with heart disease to be in better physical condition in order to increase their participation and sense of quality of life.

Supplementary Material 1. Intervention in Physiotherapy.

| Training common to both groups |        |              |        | Specific training of the experimental group                                                                             |                                                                              |        |       |        |
|--------------------------------|--------|--------------|--------|-------------------------------------------------------------------------------------------------------------------------|------------------------------------------------------------------------------|--------|-------|--------|
| Respiratory-training phase     |        |              |        | Endurance-training phase                                                                                                | Peripheral resistance-training phase                                         |        |       |        |
| 20 minutes                     |        |              |        | 10 minutes, increasing 5 minutes in each training session, until 20 minutes.                                            | 10 minutes, increasing 5 minutes in each training session, until 20 minutes. |        |       |        |
| Exercise                       | Series | Reps.        | Rest   | Exercise                                                                                                                | Exercise                                                                     | Series | Reps. | Rest   |
| Diaphragmatic breathing        | 3      | 10           | 1 min. | Walk in continue modality. Perceived exertion will be important, so we will give a modified-Borg scale to all patients. | Sit-to-stand                                                                 | 3      | 8-12  | 20 sec |
| Thoracic expansion             | 3      | 10           | 1 min. |                                                                                                                         | Shoulder bridge                                                              | 3      | 8-12  | 20 sec |
| incentive spirometry           | 1      | 10
25% LC | 1 min. |                                                                                                                         | Shoulder press                                                               | 3      | 8-12  | 20 sec |
| incentive spirometry           | 1      | 1
100% MC | 1 min. |                                                                                                                         | Biceps curl                                                                  | 3      | 8-12  | 20 sec |
| Expiratory flow techniques     |        |              | 1 min. |                                                                                                                         |                                                                              |        |       |        |
| Inspiratory muscle training    | 1      | 30% MIP      | 1 min. |                                                                                                                         |                                                                              |        |       |        |

